## 1. Abstract

The majority of acute, short-term opioid tablets prescribed following surgery go unused. In a recent analysis of post-operative orthopedic and urologic surgery data at 7 days >60% of tablets were left unused, and patients reported no intention of using them, by post-operative day 7. Disposal of unused opioid medications is important to limit diversion, misuse, and conversion to new persistent use. These are salient to the patient and others around them including children, family and friends. Though patients can flush their unused opioids, early research has shown that providing patients with disposal techniques can improve proper disposal rates. In this proposal we seek to test, through a randomized clinical trial, if providing patients with an opioid disposal kit at key post-operative times can improve the rate of self-reported disposal as compared with usual care. Using an established, automated system our primary outcome will be self-reported opioid disposal rates. We will conduct a prospective RCT amongst patients undergoing urologic surgeries, neurosurgeries, and orthopedic surgeries.

## 2. Overall objectives

The objective of this study is to use a randomized, controlled trial to test the effectiveness of mailed post-operative opioid disposal to promote safe opioid disposal following procedures in neurosurgery, orthopedics, and urology.

## 3. Aims

### *3.1 Primary outcome*

The primary outcome variable is rate of self-reported opioid disposal.

### *3.2 Secondary outcome*

The secondary outcome is self-reported number of opioid tablets used following surgery.

## 4. Background

The majority of acute, short-term opioid tablets prescribed following surgery go unused. In a recent analysis of post-operative orthopedic and urologic surgery data at 7 days >60% of tablets were left unused, and patients reported no intention of using them, by post-operative day 7. Additionally, in a sample of neurosurgery patients, 64% of patients reported having excess tablets and not disposing of them follow surgery. Disposal of unused opioid medications is important to limit diversion, misuse, and conversion to new persistent use. These are salient to the patient and others around them including children, family and friends. Though patients can flush their unused opioids, early research has shown that providing patients with disposal techniques can improve proper disposal rates.

Human behavior, and the study of behavioral economics, may provide an opportunity to improve opioid disposal after surgery but remains understudied. The concept of availability bias, or a tendency to think or act

on things which are most present in one's mind, can be tested in this context. In this proposal we seek to test, through a randomized clinical trial, if providing patients with an opioid disposal kit at key post-operative times can improve the rate of self-reported disposal as compared with usual care. Using an established, automated system our primary outcome will be self-reported opioid disposal rates. We will conduct a prospective RCT amongst patients undergoing urologic surgeries, neurosurgeries, and orthopedic surgeries.

## **5. Study design**

### *5.1 Design*

This is a two-arm, randomized, controlled trial. The study will be conducted using an automated, remote text messaging platform (Way to Health) which delivers text messaging following orthopedic, neurosurgical, and urology procedures at the University of Pennsylvania.

The study team will identify potential participants from the electronic health record at the University of Pennsylvania Health System using Penn Data Store and Clarity, an EPIC reporting database. Patients undergoing a procedure in neurosurgery, orthopedics, or urology and who are prescribed an acute opioid will receive a text message four days following their discharge. This established system obtains remote, text-messaged based consent on post-operative day four. For those consenting, patients are queried on self-reported pain intensity, ability to manage pain, use of non-opioid analgesics, use of opioid analgesics, and opioid disposal. Once a participant responds and consents on day four, the participant will be mailed an opioid disposal kit which includes an informational sheet and the chemical packet (DispoRx).

Participants will be randomly assigned to intervention or control according to calendar week of surgery in alternating weeks over a 6-week period. Participants randomized to the control arm will receive no other interventions.

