### *5.2 Study duration*

This is 6-week study.

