### *5.4 Accrual*

We estimate that a sample size of 250 participants (125 per arm) will provide at least 80% power using a conservative Bonferroni adjustment of the Type I error rate with a 2-sided  $\alpha$  of 0.025 to detect a 20% change in disposal rates. Preliminary data suggest a baseline rate of 25%.

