### *8.2 Procedures*

After providing informed consent, participants will be sent messaging on post-operative days 4, 7, 14, 21, and 28. At each time point, patients are asked to self-report pain intensity (scale 0-10, 10 being severe), ability to manage pain (scale 0-10, 10 being very able to manage), and use of non-opioid and opioid analgesics. Patients who are using opioid analgesics are asked to report quantity used, projection of future use for acute pain. Patients reporting no further use are asked about disposal (Yes or No).

Patients will be mailed opioid disposal packets, DispoRx, which are small chemical polymers which individuals can pour directly into a pill bottle. The individual shakes the bottle and the medication is deactivated, rendered unusable and can be placed safely in the trash. We will mail these packets to individuals within the first 7 days for Orthopedic and Urology and timed for 21 days for Neurosurgery.

145 Participants will be randomly assigned at the individual level to receive a disposal packet. Participants  
146 randomized to the control arm will receive no other interventions.

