## 147 **9. Analysis plan**

148 To compare sample characteristics between arms we will use t-tests or Wilcoxon rank-sum tests (F-tests or  
149 Kruskal-Wallis test) for continuous variables and Pearson chi square tests or Fisher's exact tests for categorical  
150 variables. In our primary analyses, we will compare rates of opioid disposal (baseline vs. 6-week study period).  
151 In the secondary analysis we will compare self-reported pain intensity, ability to manage pain, and opioid use.  
152 All hypothesis tests will be two-sided using a two-sided alpha of 0.025 as our threshold for statistical  
153 significance. We will use Stata and/or SAS to analyze the data.

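### Sections 5.1 and 8.2 give incompatible allocation methods; if the alternating-week rule in 5.1 is followed, the arm is not random and neither the sample size nor the analysis plan allows for it.

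*Supplement*

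**What the plan says.** Two sections of the same protocol text, dated March 18, 2021, describe how participants reach their arm.

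- Section 5.1 (Design): "Participants will be randomly assigned to intervention or control according to calendar week of surgery in alternating weeks over a 6-week period".
- Section 8.2 (Procedures): "Participants will be randomly assigned at the individual level to receive a disposal packet".

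Section 5.2 fixes the length: "This is 6-week study". Section 5.1 also places text-message consent on post-operative day 4.

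Section 5.4 (Accrual) gives the sample size: "We estimate that a sample size of 250 participants (125 per arm) will provide at least 80% power using a conservative Bonferroni adjustment", with a two-sided alpha of 0.025, "to detect a 20% change in disposal rates". It adds: "Preliminary data suggest a baseline rate of 25" per cent.

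Section 9 (Analysis plan) repeats the alpha: "All hypothesis tests will be two-sided using a two-sided alpha of 0.025 as our threshold for statistical" significance. It names t-tests, rank tests and chi-square or exact tests only for comparing sample characteristics between arms. For the primary outcome it says that disposal rates will be compared, baseline against the 6-week period, and names no test. It has no term for calendar week or clustering. The protocol describes neither sequence generation nor concealment.

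**The concern.** The two rules define different trials. Under 5.1, everyone operated on in the same week shares an arm. Under 8.2, patients from the same week are split between arms. Two teams could each follow this protocol faithfully and run different designs.

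The difference matters because strict alternation by week is not random. Once the first week's arm is set, every later arm follows from the date of surgery, and it is settled before the patient consents. Any difference between weeks, such as case mix or operating schedules, is then mixed with the effect of the kit. With three weeks per arm there is little chance for such differences to average out. A sample size and a test built for independent patients would overstate the information in the data.

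**Working it through.** **Inputs.** From 5.4: 125 per arm, control rate 25%, 20% change, two-sided alpha 0.025, power at least 80%. From 5.1 and 5.2: six calendar weeks in alternation, so 3 weeks per arm. I assume equal weeks, m = 250/6 = 41.7 patients each. No ICC is given; I use 0 to 0.02 as an assumed range.

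**Step 1: the plan's own figure.** Read the change as absolute, 25% to 45%. With z = 2.2414 (two-sided 0.025) and pooled rate 0.35:

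- z for power = [0.20 × √125 − 2.2414 × √(2 × 0.35 × 0.65)] / √(0.25 × 0.75 + 0.45 × 0.55)
- = (2.2361 − 1.5119) / 0.6595 = 1.098, so power = **86.4%**.

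For 80% power, 107 per arm are needed (117 with continuity correction). The stated figure therefore reproduces for independent patients. A relative change (25% to 30%) would give only 8.7% with 125 per arm, so the absolute reading is the one that fits.

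**Step 2: alternating weeks, power by design effect.** DE = 1 + (m − 1) × ICC, effective n per arm = 125/DE, put into the formula of step 1. This is optimistic, because the normal approximation ignores that there are only six clusters.

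| Week ICC (assumed) | DE | Effective n per arm | Power |
|---|---|---|---|
| 0 | 1.00 | 125.0 | 86.4% |
| 0.005 | 1.20 | 103.9 | 78.8% |
| 0.01 | 1.41 | 88.9 | 71.4% |
| 0.02 | 1.81 | 68.9 | 58.9% |

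Power crosses 80% at an ICC of about 0.004.

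**Step 3: alternating weeks, cluster-level t-test.** Six week-level rates leave 6 − 2 = 4 degrees of freedom, with critical value 3.495 at two-sided 0.025. The standard error of the difference is √(0.435/125 × DE), where 0.435 = 0.25 × 0.75 + 0.45 × 0.55. At ICC 0 this is 0.0590, so the noncentrality is 0.20/0.0590 = 3.39. Power from the noncentral t is:

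- ICC 0: **53.9%**
- ICC 0.01: 40.4%
- ICC 0.02: 32.0%

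The ICC 0 value is the ceiling for a non-negative ICC. The shortfall there comes entirely from having 4 degrees of freedom.

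**Step 4: type I error if the outcome test ignored weeks.** Treating week effects as random, true error = 2 × [1 − Φ(2.2414/√DE)]:

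- ICC 0.01: 2.2414/√1.407 = 1.890, error **5.9%**
- ICC 0.02: 2.2414/√1.813 = 1.664, error **9.6%**

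The nominal level is 2.5%.

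**The case against.** The strongest reply is that everything numerical depends on 5.1 being the rule in use. Section 8.2 states individual assignment and 5.4 is sized for it; on that reading the power claim is sound. This stands: a reader might infer that the sample size is simply wrong, and the documents do not support that.

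Four further inferences go too far.

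- *The chi-square and t-tests of section 9 wrongly treat patients as independent in the primary analysis.* Those tests are named for sample characteristics only. The type I errors above belong to an assumed individual-level outcome test. What the documents show is that no outcome test is named and no week term is planned.
- *Power under 5.1 is 54% or less, whatever the analysis.* That ceiling belongs to a cluster-level t-test, which the protocol does not propose. With no correlation within weeks, an individual comparison would still have 86.4%.
- *A permutation test of 3 against 3 weeks could never give p below 2/20 = 0.10.* That figure assumes 20 equally likely allocations. Strict alternation has only two possible sequences, so it does not describe 5.1, and no permutation test is planned.
- *Knowing the arm before consent has biased enrolment.* Sections 5.1, 6 and 8.1 describe identification from the health record and consent by text, with message questions and timing unchanged. Nothing says that a recruiter picks patients or that patients learn their arm before consenting. Concealment is a missing safeguard; selection bias is not demonstrated.

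None of this reconciles the two sections or makes alternation by week random.

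**Conclusion.** The point holds as an unresolved contradiction about the unit and method of allocation, and it must be fixed. Allocation is the basis for a causal comparison and cannot be repaired after enrolment.

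The consequences are conditional. If 8.2 governs, the stated power stands at 86.4%. If 5.1 governs, the comparison is not randomized, arm is confounded with week, and the stated power is secure only if the week ICC is below about 0.004 and an individual-level analysis is accepted despite having six clusters. These figures rest on equal weekly enrolment, an absolute 20-point change, and ICC values that are assumptions. The documents contain no week-to-week data from which to judge where the true ICC lies.

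**What to change.** Delete the alternating-week sentence in 5.1. State the same rule in 5.1 and 8.2: 1:1 individual randomization, with a concealed, computer-generated sequence applied after consent on day 4. Say who generates and holds the sequence. In section 9, name the primary test as a comparison of disposal between the randomized arms.

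Stratifying by specialty (orthopedics, urology, neurosurgery) and including the strata in the analysis is a reasonable option, but curing the contradiction does not require it.

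The cost is protocol wording and setting up the sequence. No extra patients are needed, since 5.4 is already sized for individual allocation. Section 5.1 already ties mailing to each participant's consent, so mailing by individual is no new burden. The protocol describes the texting platform only as delivering messages, so the study team should confirm whether it can also assign arms or whether a separate tool is needed.

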### *5.2 Study duration*

This is 6-week study.

### *5.3 Target population*

Adult (18 years or older), English speaking patients, with access to a mobile (SMS capable device) undergoing orthopedic, urologic, or a neurosurgical procedure

### *5.4 Accrual*

We estimate that a sample size of 250 participants (125 per arm) will provide at least 80% power using a conservative Bonferroni adjustment of the Type I error rate with a 2-sided  $\alpha$  of 0.025 to detect a 20% change in disposal rates. Preliminary data suggest a baseline rate of 25%.

### *5.5 Key inclusion criteria*

1) Adult (18 years or older), 2) English speaking patients, 3) access to a mobile (SMS capable device), 4) prescribed an acute opioid, 5) consenting to text message and 6) undergoing orthopedic, urologic, or a neurosurgical procedure

### *5.6 Key exclusion criteria*

1) Conditions that would make participation infeasible such as inability to provide informed consent, illiteracy or inability to speak, read, and write English or 2) not providing virtual consent

## **6. Subject recruitment**

The study team will identify potential participants from the electronic health record at the University of Pennsylvania Health System using Penn Data Store and Clarity, an EPIC reporting database.

## **7. Subject compensation**

No participants will be compensated.

## **8. Study procedures**

### *8.1 Consent*

Upon recruitment, individuals will be sent a text message via the Way to Health platform with an opportunity to consent or decline. Participants have the ability to opt-out of text messaging and the study at any point by text messaging a response of “STOP.” The current post-operative text messaging protocol has been approved by the QI IRB and has been in place with an average response rate of 50-60%. We will not change the questions or timing of messages being sent. The questions related to opioid disposal are pre-existing.

### *8.2 Procedures*

After providing informed consent, participants will be sent messaging on post-operative days 4, 7, 14, 21, and 28. At each time point, patients are asked to self-report pain intensity (scale 0-10, 10 being severe), ability to manage pain (scale 0-10, 10 being very able to manage), and use of non-opioid and opioid analgesics. Patients who are using opioid analgesics are asked to report quantity used, projection of future use for acute pain. Patients reporting no further use are asked about disposal (Yes or No).

Patients will be mailed opioid disposal packets, DispoRx, which are small chemical polymers which individuals can pour directly into a pill bottle. The individual shakes the bottle and the medication is deactivated, rendered unusable and can be placed safely in the trash. We will mail these packets to individuals within the first 7 days for Orthopedic and Urology and timed for 21 days for Neurosurgery.

145 Participants will be randomly assigned at the individual level to receive a disposal packet. Participants  
146 randomized to the control arm will receive no other interventions.

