**Q4:**

*"We just have a few more questions. [line break] Have you taken any of the following medications for your pain since your procedure (Acetaminophen, Aspirin, Ibuprofen, or Naproxen)? [Y for yes or N for no]. "*

326 LOGIC:

327 ○ If response = Y, N, yes, or no → Proceed to **Q5**

328 ○ If response ≠ Y, N, yes or no → REPLY "I'm sorry. We don't understand. Please text back Y or N."

329

330 **Q5:**

331 *"Thanks, this information helps guide our practice. It looks like you were also prescribed [opioid\_RX] for your*

332 *pain. [line break]Have you taken this medication? [Y for yes or N for no]."*

333

334 LOGIC:

335 ○ If response = Y or yes → Proceed to **Q6**

336 ○ If response = N or no → Proceed to **Q10**

337 ○ If response ≠ Y, N, yes or no → REPLY "I'm sorry. We don't understand. Please text back Y or N."

338

339 **Q6:**

340 *"Can you estimate how many pills of [opioid\_RX] you have taken since your procedure? Please text back a*

341 *number"*

342 LOGIC:

343 ○ If response = Number → Proceed to **Q7**

344 ○ If response ≠ Number → REPLY "I'm sorry. We don't understand. Please text back a number."

345

346

347 **Q7:** *"Do you have any of these pills remaining? [Y/N]"*

348 LOGIC:

349 ○ If response = Y, yes → Proceed to **Q8**

350 ○ If response = N, no Proceed to **Q10**

351 ○ If response ≠ Y, N, yes or no → REPLY: *"I'm sorry. We don't understand. Please text back Y or N."*

352

353

354 **Q8:** *"Do you plan to continue taking [opioid\_RX] to control your pain? [Y/N]"*

355 LOGIC:

356 ○ If response = Y or yes → REPLY: *"Thanks so much for your feedback! We'll check back with you in a few*

357 *days. If you have any questions or concerns about your care or health please contact your surgical team.*

358 *Have a nice day!"*

359

360 ---This patient will be texted in 1 week---

361

362  
363  
364  
365  
366  
367  
368  
369  
370  
371  
372  
373  
374  
375  
376  
377  
378  
379  
380  
381  
382  
383  
384  
385

- If response = N or no → **Move to Q9**
- If response ≠ Y, N, yes or no → REPLY: *"I'm sorry. We don't understand. Please text back Y or N."*

**Q9:** "Have you disposed of your unused %opioid% medication? [Y/N]"

LOGIC:

- If response = Y or Yes → That's great to hear. It's important to dispose of your unused medication. Just one more question for you: [line break] *"How many days did it take for your pain to improve after your procedure? Please text back a number."*

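### Disposal is recorded only for patients who reply, took the opioid, still hold pills and plan no further use, and the plan sets no denominator or rule for everyone else

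*Supplement*

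**What the plan says.** Section 3.1 defines the outcome in one sentence: "The primary outcome variable is rate of self-reported opioid disposal". It gives no denominator and no time point. Section 8.2 schedules messages on days 4, 7, 14, 21 and 28, and on the disposal question it says "Patients reporting no further use are asked about disposal (Yes or No".

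The text-message script at the end of the supplement determines who actually gets that question:

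- Script item Q5 (any opioid taken): "If response = N or no → Proceed to Q10". Item Q10 asks about days until pain improved, not about disposal.
- Script item Q7 (any pills remaining): "If response = N, no Proceed to Q10".
- Script item Q8 (plan to continue): yes ends the contact, with another text in a week. No leads to Q9.
- Script item Q9: "Have you disposed of your unused %opioid% medication".

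Section 9 states that "we will compare rates of opioid disposal", with no analysis set, no intention-to-treat statement and no handling of unasked or missing answers. Section 5.5 requires that a patient be "prescribed an acute opioid"; it does not require leftover tablets. Section 8.1 lets participants opt out at any time, says that questions and timing will stay as they are, and reports that the existing messaging "has been in place with an average response rate of 50-60" per cent. Under section 5.1 the kit is mailed after the day-4 reply and consent. Section 8.2 puts mailing within 7 days for orthopedics and urology and at 21 days for neurosurgery.

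**The concern.** Having a recorded outcome depends on later behaviour: replying, having used the drug, still holding pills and having decided to stop. After mailing, a kit could prompt a patient to stop, to empty the bottle, or to answer more or fewer texts. If the analyst divides reported disposals by patients asked, which is what the collected data invite, the two arms' denominators are formed partly by the intervention, and randomization no longer protects the comparison.

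Two routes through the script make this worse. A patient who has already disposed of every pill can truthfully say none remain, and so leaves both numerator and denominator. A patient who never took a pill may hold the whole supply and is never asked.

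**Working it through.** **1. The plan's own figure.** Inputs from section 5.4: 125 per arm, two-sided alpha 0.025, baseline 25%, a 20% change. I read the change as 20 percentage points (25% vs 45%); the relative reading (25% vs 30%) gives only 8.7% power. With pooled variance:

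Power = Φ{[0.20·√n − z·√(2·0.35·0.65)] / √(0.25·0.75 + 0.45·0.55)}, z = 2.2414.

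At n = 125: (2.2361 − 1.5119)/0.6595 = 1.098, so power is 86.4% (Fisher's exact test 83.7%). The claim of at least 80% reproduces, provided all 125 per arm have an outcome. For 80% power, 107 outcomes per arm are needed.

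**2. Power when only a share answers.** The shares are assumptions; the documents give none.

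| Share with an answer | Answers per arm | Power among those answering | Randomized per arm for 80% |
|---|---|---|---|
| 100% | 125 | 86.4% | 107 |
| 90% | 112 | 82.0% | 119 |
| 80% | 100 | 77.0% | 134 |
| 60% | 75 | 63.1% | 179 |

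If instead all 125 stay in the denominator and the rest count as not disposed, 80% answering turns 25% vs 45% into 20% vs 36% (power 72.1%, 149 per arm needed). At 60% it becomes 15% vs 27% (power 53.5%, 218 per arm).

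**3. Direction of bias.** Let p be the true disposal rate, and let a and b be the answering rates of disposers and non-disposers. The observed rate is p·a / [p·a + (1 − p)·b]. Assume 60% answering for all controls, so that the control rate is 25%.

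- No true effect, kit disposers answer at 80% and non-disposers at 60%: 0.20/(0.20 + 0.45) = 30.8%, a spurious +5.8 points.
- No true effect, kit disposers at 60% and non-disposers at 80%: 0.15/(0.15 + 0.60) = 20.0%, a spurious −5.0 points.
- True 45% in the kit arm, first pattern: 0.36/(0.36 + 0.33) = 52.2%, apparent effect 27.2 points.
- True 45%, second pattern: 0.27/(0.27 + 0.44) = 38.0%, apparent effect 13.0 points.
- Equal answering throughout: no bias.

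**4. The route out through script item Q7.** Assume that one third of disposers report no pills left and are never asked. In both arms: 0.1667/(0.1667 + 0.75) = 18.2% vs 0.30/(0.30 + 0.55) = 35.3%, a difference of 17.1 points instead of 20. If it happened only in the kit arm: 35.3% − 25% = 10.3 points.

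**5. What the unasked could hide.** Suppose that those asked show 25% vs 45%. With 80% asked, the difference among all randomized lies between 0.36 − (0.20 + 0.20) = −4 points and (0.36 + 0.20) − 0.20 = +36 points. With 60% asked the limits are 0.27 − 0.55 = −28 and 0.67 − 0.15 = +52. These limits are extreme, since some unasked patients truly have nothing to dispose of.

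**The case against.** The strongest reply is that much of this is silence, not error. A reader might infer that the plan rejects intention-to-treat. It does not: an all-randomized denominator is neither specified nor excluded. What stands is that the data are collected conditionally and nothing assigns an outcome to the rest.

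A reader might also infer that the kit acts on every condition at every contact. The documents do not support that. Item Q9 can be reached on day 4, before mailing, and with neurosurgery mailing timed for 21 days, that group's day 4, 7 and 14 answers also precede it. The exposure begins at the first contact after mailing.

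Nor does the 50–60% figure show loss after randomization. It describes the existing programme and may refer to initial response, while enrolment itself requires a reply. Retention among enrolled patients is unknown.

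Restricting the rate to patients with tablets to dispose of is also a sensible aim. That is fair, but the restriction has to be fixed before the kit can influence it, and the plan does not do so.

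Finally, every bias figure above rests on assumed answering rates, and under no true effect the artefacts of step 3 are well below the 20-point target. That stands too: bias is possible, not demonstrated.

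**Conclusion.** The point holds in this form: the primary outcome is recorded only in a conditional subgroup, the plan defines no denominator, analysis set or missing-data rule, and from the first contact after mailing the subgroup can depend on assignment. A rate among those asked can err in either direction. Its size cannot be found from the documents. Under the assumptions shown, a true 20 points could read as 10.3 to 27.2; under equal and non-informative answering there is no bias, only less power. The power statement is correct for complete answers and falls to about 77% or 63% if 80% or 60% answer. Because this concerns the primary outcome and can be mended cheaply before analysis, it should be changed.

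**What to change.** - **Analysis set.** By assigned arm, all randomized participants whose day-4 answers, given before any kit is mailed, show that they still hold tablets. Outcome: disposal reported by day 28.
- **Script.** Send item Q5 = no and item Q7 = no replies to a disposal question, and repeat it at each remaining contact through day 28. The script shows a repeat text only after item Q8 = yes, so the repeat needs stating. Amend the sentence in section 8.1 that the questions will not change. Without this step, counting unasked patients as not disposed would misclassify real disposers, possibly more often in the kit arm.
- **If the script cannot change.** Limit the set to participants with Q5 = yes and Q7 = yes on day 4 who have not already disposed, and treat a later Q7 = no as unknown, not as a failure to dispose.
- **Missing answers.** Count non-response as not disposed in the primary analysis. As sensitivity analyses, use multiple imputation (arm, specialty, day-4 answers), best- and worst-case bounds, and the responders-only rate. Report the shares asked and responding by arm.
- **Power.** Restate section 5.4 for the expected size of the day-4 set and the expected share with an answer. Because non-response counts as not disposed, the lower figures (72.1% at 80% answering, 53.5% at 60%) are the relevant guide if all 125 per arm enter the set.

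The cost is protocol wording, a small script change, modest analysis work, lower absolute disposal rates and a less favourable power statement.
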